## Abstract

**Background:**

Class III radical hysterectomy (RH III)_plus pelvic lymphadenectomy is the standard surgery for early stage cervical cancer (CC) patients, the 5 year survival rate is about 90%, but pelvic floor disorders especially bladder dysfunction are common due to damaged vessels and nerve fibers following surgery. Transcutaneous electrical stimulation (TENS) treatment has been used to treat bladder disorders for many years, but its effect on cervical cancer patients, the best treatment time point and stimulated protocol, had never been assessed. The aim of this study is to investigate the efficacy of TENS treatment on lower urinary tract symptoms (LUTS) after RH III in CC patients.

**Methods/Design:**

The study will be conducted as a clinical, multicentre, randomised controlled trial with balanced randomisation (1:1). The planned sample size is 208 participants (at 1:1 ratio, 104 subjects in each group). At 5–7 days after RH III, patients are screened according to operative and pathological findings. Enrolled participants are randomised into an intervention group (TENS plus conventional clinical care) or control group (conventional clinical care), with stratification by menopausal status (menopause vs. non-menopause) and surgical modality (laparoscopic RH or abdominal RH). Participants in both groups will be followed up at 14 days, 21 days, 28 days, 3 months, 6 months, 12 months, 18 months and 24 months after surgery. The primary endpoint is improvement rate of urination function which is defined as recovery (residual urine ≤50 ml) or improvement (residual urine 50–100 ml). Secondary endpoints include urodynamic parameter, urinary incontinence, anorectal function, pelvic function, quality of life (QOL), disease-free survival and adverse events. Primary endpoint analyses will be carried out by Cochran-Mantel-Haenszel tests taking into center effect.

**Discussion:**

To our knowledge this is the first trial to investigate the effect of TENS treatment on bladder function recovery after RH III among CC patients. This study will provide new information on TENS efficacy for bladder function recovery. Once confirmed, it may help to provide a new, non-invisive treatment for those postoperative CC patients with poor pelvic function, which would help improve their quality of life.

**Trial registration:**

The study is registered to Clinical Trials.gov (NCT02492542) on June 25, 2015.

## Background

Cervical cancer is one of the most commonly diagnosed malignant tumors among women all over the world [1]. There are an estimated 131.5 thousand newly diagnosed cervical cancer cases per year in China, accounting for 28.8% of the world’s cases. In all, 30% of cervical cancer patients are younger than 30 years [2]. With the widespread availability of cervical cancer screening, the proportion of early stage cervical cancer is increasing year by year. The standard treatment for patients with early stage cervical cancer is class III radical hysterectomy plus pelvic lymphadenectomy, with chemotherapy and/or radiotherapy supplemented as needed. The 5 year survival rate after treatment can reach as high as 90% [2]. Pelvic vessels, autonomic nerve fibers and ligaments could be affected by the resection of anterior, lateral and posterior parametrium and vaginal cuff. The unintended interruption may result in pelvic floor dysfunction including disorders of lower urinary tract, defecation disorders and sexual dysfunction. Though the cancer could be cured by the surgery, many patients may suffer from decreased quality of life due to the poor pelvic function following radical hysterectomy.

It has been reported that 70%–85% cervical cancer patients suffer from bladder dysfunction following radical hysterectomy [3, 4]. The main symptom of short-term bladder dysfunction is urinary retention (UR) while the long-term postoperative bladder disorder is urinary incontinence [5, 6]. Usually the time of indwelling urinary catheter after class III radical hysterectomy is 2 weeks, but it lasts up to 1 month in about 15% patients and even more than half a year in 3% patients because of chronic urinary retention [6, 7].

In clinical practice, doctors have tried many therapeutic methods to prevent and manage UR in patients who underwent radical hysterectomy. Among these methods, early postoperative bladder training is most commonly used, the urinary catheter is clamped and unclamped every 2–4 h to let the bladder fill and empty, aiming to exercise the detrusor contraction ability. But a recent randomized trail showed that this bladder training did not reduce the rate of UR or re-admission for bladder catheterization [8]. Some Chinese doctors use acupuncture to treat UR after radical hysterectomy with potential efficacy [9], but more studies are needed to prove its effects due to limited sample size and poor study design, moreover, acupuncture is difficult to apply, in general, due to the specialized technique. For those with chronic UR, clean intermittent catheterization or even suprapubic cystostomy is needed which are associated with frequent urinary tract infection [10].

Recently, electrical stimulation has been used to treat bladder disorders, especially for urinary retention and incontinence and the efficacy is promising [11, 12]. The electrical stimulations mostly used were transcutaneous electrical stimulation (TENS), percutaneous tibal nerve stimulation (PTNS) and sacral neuromodulation (SNM). TENS is noninvasive, easy performed and low cost compared to the other treatment options. Electrical stimulation of the sensory fibers of the pudendal nerve with low frequency (2 ~ 5HZ) evoked bladder contraction, resulting in increasing voiding efficiency, even in acute spinal transection abolished in animal models [13]. Few trials have explored the electrical stimulation for treatment of VR in cervical cancer patients [14–16], and these trails had small numbers of participants. We therefore conducted this RCT trail to verify if early postoperative TENS treatment can reduce the rate of VR in cervical cancer patients who underwent class III radical hysterectomy.

## Methods and design

### Trial design and setting

The trial is conducted as a clinical, multicentre, randomised controlled trial with balanced randomisation (1:1) to examine the efficacy of transcutaneous electrical stimulation (TENS) treatment on the recovery of urinary function among postoperative patients with early cervical cancer. After class III radical hysterectomy, participants with early cervical cancer (International Federation of Gynecology and Obstetrics [FIGO], stage Ia2, Ib1 and IIA1) will be randomly assigned to an intervention or control group. Participants will be stratified by menopausal status and surgical modality. Subjects will be recruited continuously by oncologists from gynecology departments in nine hospitals of Beijing city: Peking University People’s Hospital; Peking University First Hospital; Peking University Third Hospital; Cancer Institute and Hospital, Chinese Academy of Medical Sciences; Peking University Cancer Hospital & Institute; The General Hospital of the People’s Liberation Army; Beijing Obstetrics and Gynecology Hospital, Capital Medical University; Beijing Chaoyang Hospital, Capital Medical University; and Beijing Hospital. Figure 1 illustrates the flow diagram of the study for both the intervention and control groups.

**Fig. 1 Fig1:**
[figure not shown]
Study flow chart

### Participants

#### Inclusion criteria

Participants satisfying the following inclusion criteria were enrolled: (1) aged 18–60 years; (2) diagnosed with clinical early cervical squamous cell carcinoma (FIGO stage Ia2, Ib1 and IIA1); (3) received the surgery of class III radical hysterectomy; (4) negative resection margins indicated by biopsy and without distant metastasis as follows: lymph node (−), depth of myometrial invasion <1/2, lymphovascular space invasion (−), resection margin (−) and with G1/G2 histological differentiation; and (5) willing to participate in the study and sign informed consent.

#### Exclusion criteria

If one of the following criteria is met, patients will be excluded from the study: (1) participants who received neoadjuvant chemotherapy, radiotherapy or chemoradiotherapy before and after operation; (2) received nerve sparing surgery; (3) urinary system injury during a gynecologic operation; (4) diagnosed with ≥ stage II pelvic organ prolapse before operation; (5) preoperative moderate to severe stress urinary incontinence (pad weight testing ≥10 g); (6) preoperative urinary retention; (7) preoperative serious functional constipation or defecation disorder; and (8) participant’s inability to fully comply with study protocol due to uncontrolled epilepsy, central nervous system diseases or psychosis.

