All the enrolled subjects will be followed up at 14 days, 21 days, 28 days, 3 months, 6 months, 12 months, 18 months and 24 months after the surgical operation. Residual urine following self-urination is evaluated by B ultrasound at postoperative 14 days, 21 days, 28 days, 3 months, 6 months and 12 months. Uroflowmetry, urodynamic parameter, anorectal function and pelvic floor function are assessed at postoperative 28 days; in addition, uroflowmetry and pelvic floor function are evaluated at 3 months after surgery. Quality of life (QOL) is evaluated by European Quality of Life-5 Dimensions (EQ-5D), Prolapse/Urinary Incontinence Sexual Questionnaire short form (PISQ-12), Pelvic Floor Distress Inventory (PFDI-20) and International Consultation on Incontinence Questionnaire/Overactive Bladder Symptom Score (ICIQ/OABss). All QoL related questionnaires are required to be completed during the follow-up at 3 months, 6 months, 12 months and 24 months after surgery, except PISQ-12 at 3 months. During the follow-up at 3 months, 6 months, 12 months, 18 months and 24 months after surgery, information related with laboratory testing, gynecological examination, chest X-ray and adverse events will be collected and assessed.

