### Study endpoints

The primary endpoint is improvement rate of urination function. Based on self-urination status and residual urine evaluated by B ultrasound following catheter removal and self-urination, efficacy is classified into three levels: 1) recovery: automatic micturition is achieved by patients with residual urine ≤50 ml; 2) improvement: automatic micturition is achieved by patients with residual urine 50–100 ml; 3) invalid: automatic micturition is not achieved, or automatic micturition is achieved but with residual urine ≥100 ml. Improvement rate is calculated as follows: (the number of recovery participants + the number of improvement participants)/the total number of enrolled participants *100%.

Secondary endpoints are: (1) urodynamic parameter, including maximal uroflowmetry, micturition curve, bladder sensation, detrusor muscle stability, detrusor muscle function of contraction, stress urinary incontinence, urinary retention and lower urinary tract obstruction; (2) urinary incontinence evaluated by 1 h pad test is defined as follows: <1 g continence, 1–10 g mild incontinence, 11-30 g moderate incontinence, 31-50 g severe incontinence, >50 g extremely severe incontinence; (3) anorectal function, including rectal sensation, rectal maximum volume, reflex of rectal anal internal sphincter, reflex of rectal anal external sphincter and balloon expulsion testing; (4) pelvic function, including muscle strength of type I and type II muscle fiber of pelvic muscle, fatigue of pelvic muscle, vaginal dynamic pressure and neural reflex; (5) QOL evaluated by EQ-5D, PISQ-12, PFDI-20 and ICIQ/OABss; (6) overall survival (OS), calculated as the time from initial diagnosis to death from any cause or the date of last follow-up for surviving subjects; (7) disease-free survival (DFS), defined as the period from the date of initial diagnosis to the date of recurrence, metastasis, death due to any cause or the date of last follow-up for surviving subjects; (8) adverse events.

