### Statistical analysis

Analyses will be made using SAS statistical software (version 9.3) by a statistician in Peking University Clinical Research Institute. Data will be analyzed according to the “intent-to-treat” principle. A two-sided significance level of 5% will be used for all analyses.

Descriptive statistics will be used to summarize demographic and clinical characteristics of participants randomised to the intervention and control groups. The difference between two groups on demographic characteristics, socioeconomic status, clinical characteristics and follow-up retention rate will compared using t-tests (or Wilcoxon rank sum test) and chi-square test/Fisher’s exact test as appropriate.

Primary outcome (improvement rate of urination function in 1 year) analyses will be carried out by Cochran-Mantel-Haenszel tests taking into center effect.

The difference in urodynamic parameter, anorectal function and pelvic function between intervention and control groups will be determined using t-tests or Wilcoxon rank sum tests as appropriate. The severity of urinary incontinence will be analyzed using the Wilcoxon rank sum test. The differences in QOL (evaluated by EQ-5D, PISQ-12, PFDI-20 and ICIQ/OABss) between intervention and control group will be determined using repeated measure analysis of variance (ANOVA). DFS and OS survival curves will be calculated using the Kaplan-Meier method, and compared using the log-rank test. Cox proportional hazards models will also be used to calculate hazard ratio and 95% confidence interval, with other risk factors (such as cancer stage and tumor localization) as covariates.

The incidence of adverse events between 2 groups will be compared with the chi-square test/Fisher’s exact test. Descriptive statistics will be used to summarize incidence rates of adverse events and serious adverse events.

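### Incontinence grade and three quality-of-life and symptom questionnaires are compared on post-operative values alone, although a baseline is required at screening (pad weight) or cheap to add (EQ-5D, PFDI-20, ICIQ/OABss)

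*Protocol article*

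**What the plan says.** **Eligibility.** In the Exclusion criteria, item 5 removes women with "preoperative moderate to severe stress urinary incontinence (pad weight testing ≥10 g". Values below 10 g are therefore admitted, and applying the criterion as worded needs a pre-operative pad weight.

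**Endpoint scale.** Study endpoints grades the 1 h pad test as "<1 g continence, 1–10 g mild incontinence, 11-30 g moderate incontinence", followed by two heavier grades. The grade takes no account of the pre-operative value.

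**Schedule.** Initial screening, assessment and follow-up says "All QoL related questionnaires are required to be completed during the follow-up at 3 months, 6 months, 12 months and 24 months after surgery", with PISQ-12 left out at 3 months. Table 1 agrees: its baseline column is filled for laboratory tests and imaging but empty for EQ-5D, PFDI-20 and ICIQ/OABss. The table has no row for the pad test at any visit.

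**Analysis.** Statistical analysis states "The severity of urinary incontinence will be analyzed using the Wilcoxon rank sum test". Quality-of-life scores go into a repeated-measures ANOVA. Covariates are named only for the Cox models. Randomisation is stratified by menopausal status and surgical modality, not by earlier symptoms.

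**The concern.** Women enter with different degrees of leakage and different quality of life. Where those differences persist after surgery, they widen the spread of the post-operative scores and make an effect of TENS harder to see. A woman with a pad weight of 5 g before surgery and 5 g after it is graded the same as one who went from 0 g to 5 g.

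A baseline covariate removes the part of this spread that it predicts. It also corrects for any chance difference between arms in earlier symptoms. The plan uses no such covariate. For incontinence the value should already exist from screening, and for the questionnaires none is collected. At stake is precision on secondary endpoints that lie close to the trial's aim, since the Background names incontinence as the main long-term bladder problem after this operation.

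**Working it through.** **1. The plan's own figure.** Inputs from Sample size consideration: 70% v 50%, 80% power, two-sided 0.05, 10% drop-out. With pooled variance and no continuity correction:

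n = [1.960·√(2·0.6·0.4) + 0.8416·√(0.7·0.3 + 0.5·0.5)]² / 0.2² = (1.358 + 0.571)² / 0.04 = 93 per arm.

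93 / 0.9 = 103.3, rounded up to 104 per arm, or 208 in total. The stated size reproduces. It concerns the primary endpoint only and does not change below.

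**2. Precision given up.** For a continuous score analysed in a linear model, adjusting for a baseline with correlation r to the outcome (one visit, or the mean over visits) leaves a fraction 1 − r² of the variance. This is equivalent to multiplying the sample by 1/(1 − r²). The unadjusted difference detectable with 80% power and 93 evaluable per arm is (1.960 + 0.8416)·√(2/93) = 0.41 SD. Adjustment multiplies it by √(1 − r²). All values of r are assumptions.

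| r | 1 − r² | 1/(1 − r²) | Equivalent gain in women | Detectable difference |
|---|---|---|---|---|
| 0 | 1.00 | 1.00 | 0% | 0.41 SD |
| 0.1 | 0.99 | 1.01 | 1% | 0.41 SD |
| 0.2 | 0.96 | 1.04 | 4% | 0.40 SD |
| 0.4 | 0.84 | 1.19 | 19% | 0.38 SD |
| 0.6 | 0.64 | 1.56 | 56% | 0.33 SD |

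The pad grade has five ordered levels, so for it the table is only a guide.

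**3. Chance imbalance.** Let p be the share of women with an earlier symptom (assumed; not in the article). With 104 per arm, the SD of the difference in shares is √(2p(1 − p)/104).

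| p | SD | 95% range | Chance of a gap of 10 points or more |
|---|---|---|---|
| 10% | 4.2 points | ±8.2 points | 2% |
| 20% | 5.5 points | ±10.9 points | 7% |
| 30% | 6.4 points | ±12.5 points | 12% |

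**4. The cut-points side by side.** The exclusion treats 10 g as the start of moderate leakage. The endpoint scale puts 10 g in the mild band and starts moderate at 11 g. The admitted range that overlaps the mild grade is therefore 1 g to just under 10 g, and the status of 10 g itself differs between the two sections.

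**The case against.** **No bias.** Randomisation comes before every outcome, so earlier symptoms are balanced in expectation. The Wilcoxon test is valid, and its error rate already allows for chance imbalance. This stands: the loss is in efficiency, not validity.

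**The primary endpoint is protected.** Women with "preoperative urinary retention" are excluded and the sample size reproduces. This also stands.

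**The gain may be small.** Major surgery lies between baseline and outcome, and the Background reports bladder dysfunction in 70%–85% of patients afterwards. Recall a week after surgery adds error, and the exclusion narrows the range of pad weight. Each of these could lower r, and at r = 0.1–0.2 the gain is only 1%–4%. This stands as a limit on size.

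**Covariates belong to the SAP, and the pad weight may be on file.** This stands in part. With no pad-test row, Table 1 cannot show whether the value is kept, and medical history may record symptoms. But the article itself fixes the questionnaire schedule without a baseline and names the tests. No SAP can adjust for a score that was never taken.

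**Stronger readings.** A reader might infer that the trial fails because it cannot separate new from old dysfunction. The documents do not support this: the aim is a comparison of TENS with control, and no endpoint claims new-onset incidence. A reader might also extend the point to prolapse ("diagnosed with ≥ stage II pelvic organ prolapse before operation") or constipation ("preoperative serious functional constipation or defecation disorder"), since milder forms are admitted. Neither prolapse stage nor constipation is a listed endpoint. Nor is the lack of baseline urodynamic, anorectal or pelvic-muscle tests pressed here: screening takes place 5–7 days after surgery, so that visit cannot supply a pre-operative functional measurement.

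**Conclusion.** The point holds as one of precision on secondary endpoints. The incontinence comparison has no adjustment for a pad weight that eligibility requires. The EQ-5D, PFDI-20 and ICIQ/OABss comparisons cannot be adjusted for a same-scale baseline, because none is scheduled.

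For continuous scores the loss runs from about 1% to 56% in equivalent sample size over assumed correlations of 0.1 to 0.6. The documents do not allow a narrower range, and the upper end should not be presented as expected. The chance-imbalance figures likewise rest on assumed prevalences of 10%–30%. The primary endpoint and the total of 208 are unaffected. This is a modest improvement, worth making because it costs little. The disagreement over 10 g is a separate inconsistency, which stands whatever the correlation.

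**What to change.** 1. **Pad weight.** Record the pre-operative value used for exclusion item 5 and adjust the incontinence comparison for it. Use either a Wilcoxon test stratified by <1 g v 1 to <10 g, or a proportional-odds model with pre-operative pad weight as covariate. Cost: one case-report field and a sentence in the analysis section. This assumes that every woman has a value on record. If a centre tested only women reporting leakage, a rule for the untested must be stated in advance.

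2. **Questionnaires.** Give EQ-5D, PFDI-20 and ICIQ/OABss once at the existing baseline visit, worded to refer to the weeks before surgery and completed before randomisation. Use each as a covariate in its own repeated-measures analysis. Cost: three short forms at a visit that already takes place. The downside is recall error, which lowers the gain but cannot depend on allocation. Completing the forms before randomisation matters because participants are not blinded.

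3. **Cut-point.** Reconcile the classification of 10 g between Exclusion criteria and Study endpoints. Cost: wording only.

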### Randomisation and blinding

Central randomisation via interactive web response system will be carried out by Peking University Clinical Research Institute, which is independent of the trial administration office. The allocation sequence is computer-generated 1:1 with dynamic randomisation system using minimization. Randomisation is conducted with varying block size and will be stratified by menopausal status (menopause vs. non-menopause) and surgical modality (laparoscopic radical hysterectomy or abdominal radical hysterectomy). Intervention assignment cannot be blinded for the participants and investigators due to device stimulation and blank control.

### Intervention

All participants who are assigned to the intervention group will receive TENS treatment on the basis of conventional clinical care. The stimulation treatment starts 7 days (±2 days) after radical hysterectomy. Participants receive TENS treatment twice daily for 14 days (28 treatment sessions), and those patients with residual urine >100 ml at 14 days post-operation will take an additional 7 day stimulation treatment (14 treatment sessions). Patients are placed in a supine decubital position. The electric parameters used in each session are homogeneous: current type: functional electrical stimulation; frequency: 1/4/1 Hz; pulse duration: 270/230/270 μs; time: 30 min; surface electrode: 50*50 MM adhesive electrode; stimulation intensity: maximal level tolerable without pain, usually less than 100 mA. One electrode is placed in the S3 region and the other one is crossed on the skin and fixed at the bladder area.

All subjects who are assigned to the control group will receive only conventional clinical care. With the exception of TENS, intervention and control groups have the same study procedures throughout the entire study. The catheter is removed while residual urine is less than 100 ml at 14 days, 21 days or 28 days after surgery. Catheter removal timing is determined according to the recovery of participants if residual urine is >100 ml at 28 days post-operation.

